### Data sources

The main data source for this project is the CPRD. Cause-specific mortality from linked ONS data is more accurate than CPRD data on mortality from general practices.^13^ Therefore, we will use the ONS data to identify date and cause of death and test our hypotheses relating to mortality using data from linked practices only. We will also be using the Index of Multiple Deprivation (IMD) in order to define socioeconomic position, which is listed as a covariate in our analysis.

### Study size

table 3 details the expected number of events for the event used to define the start of follow-up with the minimum sample size and detectable HR (α=0.05, β=0.80) for the Cox regression analysis of cohorts B and C. The minimum detectable HR is taken to be the detectable HR for the smallest exposed group tested against the control group. The minimum sample size is the sum of patients in the smallest exposed group and the control group. It is difficult to provide such details for cohort A due to its novel design that includes patients who are ‘at risk’ of the condition the treatment is used for. We can however consider the expected number of events listed for cohort B to be conservative estimates for the sample size of cohort A as all patients receiving treatment are included in cohort A by definition. This study will involve a large sample of data and has considerable power to detect even relatively small effects. Therefore, our statistical power will be more than adequate to test all of our proposed hypotheses, even under highly conservative Bonferroni corrections. Further details concerning the sample size and detectable HRs (α=0.05, β=0.80) for specific comparisons within cohorts B and C can be found in online supplementary files 6 and 7. Further details concerning the expected number of events, including at the drug subclass level, can be found in online supplementary file 8.

**Table 3 BMJOPEN2016012044TB3:** The expected number of events for the event used to define the start of follow-up presented with the minimum sample size and detectable HR (α=0.05, β=0.80) for the Cox regression analysis of cohorts B and C

Cohort	Start of follow-up	Expected number of events	Minimum sample size	Minimum detectable HR
B	Treatment for hypertension	1 018 519	269 808	0.968
	Treatment for hypercholesterolaemia	808 687	788 479	0.844
	Treatment for type 2 diabetes	200 800	158 775	0.943
C	Diagnosis of dementia (AD and NADD)	105 471	105 471	0.931
	Diagnosis of PD	20 686	20 686	0.870
	Diagnosis of ALS	2227	2227	0.600

AD, Alzheimer's disease; ALS, amyotrophic lateral sclerosis; NADD, Non-Alzheimer's disease dementias.

10.1136/bmjopen-2016-012044.supp6supplementary file

10.1136/bmjopen-2016-012044.supp7supplementary file

10.1136/bmjopen-2016-012044.supp8supplementary file

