**Ethics and dissemination:**

This protocol has been approved by the CPRD's Independent Scientific Advisory Committee (ISAC). We will publish the results of the study as open-access peer-reviewed publications and disseminate findings through national and international conferences as are appropriate.

Strengths and limitations of this studyThis study will involve a large sample of data and has considerable power to detect even relatively small effects, even under highly conservative Bonferroni corrections. For example, the sample to assess the progression of dementia contains 105 471 patients and has a minimum detectable HR of 0.931.We plan to use four different statistical methods in our analysis, which have different approaches for modelling confounding. By doing this, we will be able to assess the merits of each method in the given situation in order to minimise confounding.Dementia is a heterogeneous outcome, and electronic codes used to define cases in primary care may not be as accurate as cases in clinical cohorts. We will undertake sensitivity analyses to explore how this may affect our results.

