### Multiple testing

We will account for multiple testing using permutation analysis where appropriate. A portion of the data included in this project was previously used in a study investigating the association of α-adrenoceptor blocking drugs and angiotensin-II receptor antagonists with AD and non-AD dementias.^19^ We anticipate the overlap between our study and this previous study to be around 4% for each of cohorts A and B and 9% for cohort C. The authors acknowledge that this might be a concern for multiple testing, however wish to highlight that the analyses conducted in this study will differ from those used before.

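### The claim of ample power for all hypotheses under Bonferroni correction rests on hazard ratios computed at α=0.05, and the ALS figure of 0.600 does not fit it even uncorrected

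*Protocol article*

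**What the plan says.** Table 3 of the protocol article (Study size) is captioned as giving the "minimum sample size and detectable HR (α=0.05, β=0.80) for the Cox regression analysis of cohorts B and C". The text points to supplementary files for more, in the same terms: "Further details concerning the sample size and detectable HRs (α=0.05, β=0.80) for specific comparisons within cohorts B and C". Each tabulated value is a worst case: "The minimum detectable HR is taken to be the detectable HR for the smallest exposed group tested against the control group". The ALS row reads "Diagnosis of ALS 2227 2227 0.600".

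From this the section concludes that "our statistical power will be more than adequate to test all of our proposed hypotheses, even under highly conservative Bonferroni corrections". The strengths box after the abstract says that the study "has considerable power to detect even relatively small effects, even under highly conservative Bonferroni corrections", and illustrates it with the dementia progression sample of 105 471 patients and an HR of 0.931. The Multiple testing section says: "We will account for multiple testing using permutation analysis where appropriate". None of these places gives a number of tests or a corrected significance level.

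**The concern.** The sentence asserts two things: that the study can detect relatively small effects, and that this holds for every hypothesis after a conservative correction. The figures offered in support are all uncorrected, so they cannot show the second. The ALS row does not fit the first, because an HR of 0.600 is a large effect on survival.

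ALS is one of the four diseases named in the Objectives and has its own progression cohort in Table 1. If the power statement is taken at face value, a null result there, or in the smallest drug subclasses, could be read as evidence of no effect when the comparison could only have detected a large one. The stated purpose of the work is to prioritise drugs for later trials, so that difference matters.

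**Working it through.** **Inputs.** From Table 3, the detectable HRs at "α=0.05, β=0.80": hypertension 0.968, hypercholesterolaemia 0.844, type 2 diabetes 0.943 (cohort B); dementia 0.931, PD 0.870, ALS 0.600 (cohort C). I take α as two-sided, since sidedness is not stated, and read the second figure as 80% power.

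**Reproducing 0.600.** It cannot be rebuilt forward, because the exposed share p and the number of deaths d are not in the article. Solving backwards with the Schoenfeld formula:

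d·p·(1−p) = (1.960 + 0.842)² / (ln 0.600)² ≈ 30.1

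Among 2227 patients this corresponds to about 31 exposed if all die, 41 if 75% die and 62 if 50% die. That is plausible for a small exposed group, so the figure is not shown to be wrong.

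**Before any correction.** With the information implied by 0.600, power is Φ(2.802 × |ln HR| / |ln 0.600| − 1.960). This gives 50% at HR 0.70, 23% at HR 0.80 and 8% at HR 0.90.

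**Number of tests (my counts; the article gives none).**
- m=9: cohort C, 3 disease groups × 3 treatments, one exposure definition.
- m=18: cohort C with both exposure definitions, 3 × 3 × 2.
- m=94: one statistical method across all cohorts. Cohort A 3 × 4 = 12; cohort B 16 non-control subclasses in Box 1 (9 + 5 + 2) × 4 diseases = 64; cohort C 18. Total 12 + 64 + 18 = 94.

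**Rescaling.** The exposed share and event count cancel, so Table 3 is enough:

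ln HR(corrected) = ln HR(Table 3) × (z + 0.842) / (1.960 + 0.842), where z is the normal quantile at 1 − 0.05/(2m).

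| | m=1 | m=9 | m=18 | m=94 |
|---|---|---|---|---|
| z | 1.960 | 2.773 | 2.991 | 3.464 |
| Factor | 1.000 | 1.290 | 1.368 | 1.537 |
| ALS | 0.600 | 0.517 | 0.497 | 0.456 |
| PD | 0.870 | 0.836 | 0.827 | 0.807 |
| Hypercholesterolaemia, smallest subclass | 0.844 | 0.803 | 0.793 | 0.771 |
| Dementia | 0.931 | 0.912 | 0.907 | 0.896 |
| Type 2 diabetes | 0.943 | 0.927 | 0.923 | 0.914 |
| Hypertension | 0.968 | 0.959 | 0.956 | 0.951 |
| Power at the Table 3 HR | 80% | 51% | 42% | 25% |

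Example: ALS at m=18 is exp(1.368 × ln 0.600) = exp(−0.699) = 0.497. Under the same correction, ALS power at HR 0.80 falls from 23% to 4%.

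**The case against.** The strongest reply is that the article sets no target HR, so the conflict is with wording rather than with a number. The ALS figure is openly printed and is by definition the worst case, so other ALS exposures may do better. All of this is true. An outer limit shows how much better: if all 2227 ALS patients died and exposure were split 1:1, the detectable HR would be exp(−2.802/√(2227/4)) = 0.888 uncorrected, 0.850 at m=18 and 0.833 at m=94. But the claim covers all hypotheses, and the worst case is one of them.

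The strengths-box example also survives in substance. Dementia moves only from 0.931 to 0.896 under 94 tests; the defect is that an uncorrected figure illustrates a claim about correction.

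Three stronger readings are tempting, and the documents do not support them.
- A reader might infer that Study size and Multiple testing plan different corrections. They do not conflict: Bonferroni appears as a conservative bound and permutation as the planned method. Permutation that respects the correlation between tests is generally no more stringent, so power shown under Bonferroni would cover it.
- A reader might infer that Table 3 is miscalculated, for example through its event counts. The inputs needed to show that for the cohort C rows are not in the article, and 0.600 is plausible as it stands.
- A reader might take 94 as the protocol's own number of tests. No test family is defined, so 94 is one assumption in a range.

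Finally, nothing in the article says that null ALS results will be read as no effect. That is a risk created by the wording, not a stated plan.

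**Conclusion.** The concern holds as an overstated power property. Every detectable HR given in the article, and those in supplementary files 6 and 7 as it describes them, is at α=0.05, so none of them shows power under Bonferroni. For the smallest ALS exposure, the claim to detect relatively small effects fails before correction. After correction, 80% power there needs a hazard reduction of about 48% to 54% (HR 0.517 to 0.456). PD and the smallest lipid subclass weaken to between 0.836 and 0.771 over the same range. The dementia, type 2 diabetes and hypertension rows, as tabulated, remain at about 0.90 or nearer to 1, so the claim is defensible for them.

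The sizes assume two-sided testing, 80% power, Table 3 taken as given, and 9 to 94 tests. The direction does not depend on the number of tests chosen.

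**What to change.** State the number of tests to which the power claim refers, and add a column to Table 3 with detectable HRs at the corrected α. Bonferroni can stay as the bound; the planned permutation method need not change. Quote the strengths-box example at the corrected α.

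Restrict the wording about all hypotheses and relatively small effects to the comparisons that support it (the dementia, hypertension and type 2 diabetes rows as tabulated). State that ALS and the smallest subclasses can detect only larger effects, so null results there are inconclusive.

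The cost is text and a recalculation. Design, data and analyses are untouched, but the published power figures become less favourable.

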#### Covariates

We will match all covariates on date of birth, sex, year of index date and years of recorded history in the database before the index date. The covariates we will include in our analyses are body mass index, smoking status, alcohol consumption, a postcode-based measure of socioeconomic position, previous history of coronary-artery disease, previous coronary-bypass surgery and cerebrovascular disease including stroke. We will also control for other major chronic illness (including cancer, arthritis) using the Charlson Index^11^
^12^ and for consultation rate, calculated by dividing the total number of clinic visits prior to the index date by the length of each patient's follow-up. If there are missing data in the covariates, we will consider using multiple imputation. Unfortunately not all covariates of interest, such as exercise, are recorded within the CPRD, and this may lead to unmeasured confounding. We hope to minimise this confounding by using methods, such as instrumental variable analysis, which can account for it to some degree.

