#### Instrumental variable analysis

In our third analysis, we will estimate the effects: (1) treatment or no treatment and (2) the specific subclass of medication prescribed, using physicians' prescribing preferences as instruments for the prescriptions the GPs issue to their patients. We cannot directly measure the physicians' preferences; therefore, we will use the prescriptions they issued to their previous patients as a proxy for their preferences. For example, if the instrument were based on just one previous prescription, physicians who previously prescribed the treatment therapy would be categorised as a ‘treatment prescriber’ otherwise they would be categorised as a ‘control prescriber’. As with our previous studies we will use seven prior prescriptions to improve the strength of the instruments.^25–27^ Using multiple prior prescriptions will maximise power. We will report risk differences in the outcomes using additive structural mean models estimated via the generalised method of moments.^28–30^ We will categorise each of the adverse event outcomes as occurring within 3, 6, 9, 12, 24 and 48 months of index date. Methods for estimating survival models using instrumental variables are not well developed. Therefore, we will explore potential instrumental variable survival models in a secondary analysis.^31^

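### The power claim covers all hypotheses, but only the Cox analyses of cohorts B and C are sized; the instrumental variable analysis of cohorts A and B is not, and any imperfect instrument gives it less power

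*Protocol article*

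**What the plan says.** Table 3 in the Study size section gives minimum detectable hazard ratios "for the Cox regression analysis of cohorts B and C". For cohort B these are 0.968 (hypertension), 0.844 (hypercholesterolaemia) and 0.943 (type 2 diabetes). They refer to the least favourable contrast: "The minimum detectable HR is taken to be the detectable HR for the smallest exposed group tested against the control group". Cohort A has no such figures. Supplementary files 6 and 7 are described as giving further hazard ratios for cohorts B and C, so on that description they hold no IV sizing either.

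From this the section concludes that "our statistical power will be more than adequate to test all of our proposed hypotheses", and adds that this holds even after Bonferroni correction. The strengths and limitations list after the Abstract repeats the message about power and Bonferroni.

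Table 1 lists IV analysis for cohorts A and B but not for cohort C. The Covariates section gives it a specific job: "We hope to minimise this confounding by using methods, such as instrumental variable analysis, which can account for it to some degree". The Confounding section intends to compare the four methods so that residual confounding becomes visible. The Instrumental variable analysis section bases the instrument on seven prior prescriptions, reports risk differences for outcomes within 3 to 48 months, and states no instrument strength and no detectable effect.

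**The concern.** A conclusion about all hypotheses is drawn from a calculation for one of the four methods. The method left out is the one whose precision differs most from Cox regression on the same data, because IV uses only the part of treatment variation that the instrument explains.

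What is at stake is how the methods are read against each other. If the IV interval is wide enough to contain both no effect and the Cox estimate, then agreement with Cox, or a non-significant IV result, says little about unmeasured confounding. A reader who has been told that power is more than adequate throughout could take it as reassurance.

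**Working it through.** **Inputs from the article.** α=0.05, taken as two-sided because the sidedness is not stated. The printed β=0.80 is read as 80% power. The cohort B hazard ratios are 0.968, 0.844 and 0.943.

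**Input not in the article.** The instrument–treatment correlation r. It is assumed, and a range is shown.

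**1. Can Table 3 be reproduced?** By Schoenfeld's formula, events × p(1−p) = (1.960 + 0.842)² / (ln HR)², where p is the exposed share. This requires about 7420, 273 and 2279 for the three hazard ratios. At a 1:1 split that is 29 682, 1092 and 9115 events. The article gives neither the smallest group's share nor the outcome event counts (its events column counts cohort entries), so the tabulated hazard ratios can be neither confirmed nor refuted. They are taken as given below.

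**2. Power of IV where Cox has 80%.** The large-sample IV variance is about the conventional variance divided by r². The non-centrality 1.960 + 0.842 = 2.802 therefore becomes 2.802r, and

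power = Φ(2.802r − 1.960) + Φ(−2.802r − 1.960).

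**3. Hazard ratio at which IV would reach 80%.** On the log scale the detectable effect grows by 1/r, so it is HR^(1/r). For hypertension at r=0.2 this is 0.968⁵ = 0.850.

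| r (assumed) | IV power at the Table 3 HR | Hypertension | Hypercholesterolaemia | Type 2 diabetes |
|---|---|---|---|---|
| 0.1 | 5.9% | 0.722 | 0.183 | 0.556 |
| 0.2 | 8.7% | 0.850 | 0.428 | 0.746 |
| 0.3 | 13.4% | 0.897 | 0.568 | 0.822 |
| 0.5 | 28.8% | 0.937 | 0.712 | 0.889 |
| 0.7 | 50% | 0.955 | 0.785 | 0.920 |
| 0.9 | 71% | 0.965 | 0.828 | 0.937 |

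The last three columns are the hazard ratios for 80% IV power. The most extreme are only rough, since the scaling is a local approximation.

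**4. Interval width.** At the Table 3 hazard ratio the IV 95% half-width is (1.960/2.802)/r = 0.70/r times |ln HR|. An interval centred on that effect excludes no effect only if r exceeds about 0.70. Larger effects need a weaker instrument.

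**5. The 48-month window.** The non-centrality is multiplied by the square root of the fraction of events retained. If the window held half the events (an assumption), power would be 6.8% at r=0.2 and 16.8% at r=0.5.

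**6. Simulation check.** Two-stage least squares on a binary outcome was simulated with 20 000 patients, 20% exposed, 5% risk, an instrument built from seven prior prescriptions, and 1500 replicates. Realised correlations of 0.19 and 0.44 gave IV power of 9% and 25%, with conventional power of 85% and 86%. This agrees with the formula.

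All these figures are at α=0.05. A Bonferroni correction would lower them.

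**The case against.** The strongest reply is that the benchmark is close to circular. The minimum detectable hazard ratio is by definition where Cox has 80% power, so any less efficient method falls below 80% there. The plan names no target effect, and Table 3 describes the worst contrast for each treatment. That stands: falling short at those hazard ratios does not make IV inadequate for larger effects or for larger groups.

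It also stands that no document gives r. A reader might infer that IV power simply is 9% to 29%. That holds only if r lies between 0.2 and 0.5, and values from about 6% to 71% follow from r of 0.1 to 0.9. Nor can these figures be carried to cohort A, which has no tabulated hazard ratios, or to cohort C, which has no IV analysis.

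A reader might also take "Using multiple prior prescriptions will maximise power" as a promise of adequate power. In context it justifies using several prior prescriptions rather than one, and it is not a fault. The 48-month limit applies to the main IV analysis; IV survival models are planned as a secondary exploration.

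Finally, the plan is hedged about what IV can achieve, it will weigh each method on its merits where results differ, and first-stage detail may properly sit in an analysis plan that is not shown. None of this supports the power sentence itself, which is stated in the article, covers every hypothesis and rests on Cox figures alone.

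**Conclusion.** The point holds as one of an unsupported claim. The article sizes Cox regression in cohorts B and C and extends the conclusion to analyses it has not sized. That IV has less than 80% power at the cohort B hazard ratios needs no assumed value, only that the instrument is imperfect. It uses the large-sample variance relation and the same events as Cox. The size of the loss does depend on the unstated r.

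For r of 0.2 to 0.5, IV would reach 80% power at hazard ratios of roughly 0.85 to 0.94 for hypertension, 0.43 to 0.71 for hypercholesterolaemia and 0.75 to 0.89 for type 2 diabetes. It may therefore be informative for some contrasts and not for others. Because IV reports risk differences in fixed windows, expressing its power at a hazard ratio is an approximation, and probably one that flatters it.

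A reader might go further and conclude that IV is useless throughout, or that Table 3 is miscalculated. The documents support neither: instrument strength and group sizes are not given, and the tabulated hazard ratios cannot be checked from the article.

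**What to change.** Limit the power statements in the Study size section and in the strengths and limitations list to the Cox analyses.

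Before outcomes are examined, compute instrument strength for each cohort A and B contrast from the exposure data, and state the risk difference at 48 months that each IV analysis could detect.

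Add a reading rule. Express the Cox result as a 48-month risk difference. Where the expected IV interval could not separate that result from no effect, do not count agreement or non-significance of the IV estimate as evidence against confounding.

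The cost is a first-stage calculation on exposure data and a less favourable power statement. No patients or data are added.

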### Bias

There are three main sources of bias in our results: ascertainment bias, collider bias and immortal time bias. To overcome ascertainment bias, we will control for consultation rate in our analyses because people who have more chronic conditions such as hypertension, diabetes or renal insufficiency may have higher rates of consultation, which may also increase the opportunity for recording other diagnoses such as dementia. Collider bias could occur if we conditioned on events that happened as a result of the prescription the patient was issued. To prevent this form of bias from affecting our results, we will define each covariate using data inputted prior to the index date.^14^ Finally, we will minimise the risk of immortal time bias in two ways. First, to prevent misclassified immortal time, we will define exposures based on the first prescription observed in the database^10^ and use an intention-to-treat analysis. Second, to minimise immortal time, we will follow-up patients (exposed and unexposed) from a consistent index date. This will be a test result or a read code indicating diagnosis where possible;^15^ however, to capture all relevant patients, we will allow those receiving treatment without a recorded diagnosis to be included.

